### Secondary endpoints

Secondary outcomes are changes from baseline to week 8 in each intervention period as follows: (1) NT-proBNP and BNP levels; (2) the levels of biomarkers related to frequently and short time peritoneal equilibration test (FAST PET) [12] (ultrafiltration volume, sodium, potassium, glucose, urea nitrogen, creatinine, uric acid, protein, interleukin-6, cancer antigen 125, and drained solution-to-serum creatinine ratio); (3) the levels of biomarkers related to 24-h urine collection (urine volume, sodium, potassium, glucose, urea nitrogen, creatinine, uric acid, urine protein, and urea and creatinine clearance); (4) the levels of anemia-related factors (hemoglobin, hematocrit, ferritin, and transferrin saturation); (5) body weight, blood pressure and, body composition (intracellular and extracellular fluid volume). Details of FAST PET are shown in Supplementary Table 2. Urine kidney injury molecule 1 (KIM-1) levels will be compared at week 8 in each intervention period. Adverse events will be also evaluated during the study period.

### Sample size calculation

Our preliminary data revealed an average increase in the daily ultrafiltration volume from the glucose-based PD solution of 90 mL/day in five patients on PD who received 10 mg of empagliflozin and used at least 3 L/day glucose-based PD solution. An increase in the ultrafiltration volume of 90 mL/day is associated with an 18% reduction in the risk of death [4], which appears to be clinically significant. Based on the Osaka University cohort of patients on PD, the between-subject standard deviation (SD) of the change in the ultrafiltration volume was conservatively estimated at 150 mL (actual between-subject SD of the cohort was 114 mL), and the ratio of the between-subject SD to the within-subject SD was 1:1. We calculated that 30 patients completing the study would provide 90% power (at α = 0.05, two-sided) to detect a 90 mL difference in the ultrafiltration volume between empagliflozin and placebo. The sample size was set at 36 subjects to compensate for potential dropouts.

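### The stated 90% power does not follow from the stated SDs: a within-subject SD of 150 mL gives 30 completers about 61% power to detect 90 mL

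*Protocol article*

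**What the plan says.** All the inputs and the result are in one paragraph of the protocol article, Methods, Sample size calculation.

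- **Variability:** "the between-subject standard deviation (SD) of the change in the ultrafiltration volume was conservatively estimated at 150 mL". A parenthesis adds that the "actual between-subject SD of the cohort was 114 mL".
- **Variance split:** "the ratio of the between-subject SD to the within-subject SD was 1:1".
- **Target and test:** 90% power "to detect a 90 mL difference in the ultrafiltration volume between empagliflozin and placebo", "at α = 0.05, two-sided".
- **Result:** "We calculated that 30 patients completing the study would provide 90% power". The number randomised is then raised to 36 to allow for dropout.

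The Intervention periods section describes a two-period crossover in which every patient receives both treatments. The Primary endpoint section defines the outcome as the change from baseline to week 8 within each period. The article names no sample-size formula and gives no separate SD for the within-patient treatment difference.

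**The concern.** In a crossover, power depends on the within-subject SD, because the between-subject component cancels when each patient is compared with himself or herself. The paragraph fixes the within-subject SD indirectly: 150 mL between subjects at a ratio of 1:1 gives 150 mL within subjects. A 90 mL effect is only 0.6 of that SD (90/150), and 30 patients looked too few for 90% power.

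The 30 completers and the target of 36 rest on this paragraph. No interim analysis is planned, and the article describes no re-estimation of sample size, so nothing described there would bring an error to light during the trial. If the inputs are right as labelled, a true 90 mL effect, which the section treats as clinically important, would be missed about 39% of the time (100 − 61). A reader of the protocol would expect 10%. A null result could then be taken as stronger evidence against a useful effect than it is.

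**Working it through.** **Inputs** (all from Sample size calculation unless noted)

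- Difference δ = 90 mL; α = 0.05 two-sided; n = 30 completers in total; stated power 90%.
- Between-subject SD 150 mL; ratio 1:1, so within-subject SD σ_w = 150 mL.
- Two-treatment, two-period crossover with 1:1 sequences (Study design, Randomization, Intervention periods).

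**Formulas**

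- SD of the within-patient treatment difference: SD_d = √2 × σ_w.
- Standard error: SD_d/√n.
- Power: non-central t with n − 2 df and non-centrality δ√n/SD_d, checked against the normal approximation.
- Normal-approximation sample size: n = (1.960 + 1.282)² × SD_d²/δ².

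**Step 1. Can the plan's own figure be reproduced?** It can if SD_d itself is 150 mL (σ_w = 150/√2 ≈ 106 mL):

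- n = (3.242)² × 150²/90² = 29.2, so 30.
- Power with 30: 90.8% (normal), 88.7% (t, 28 df).
- By t-test, 90% needs 32 completers, or an SD_d of 146.8 mL or less with 30.

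**Step 2. Inputs as labelled.** SD_d = √2 × 150 = 212.1 mL.

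- n = (3.242)² × 212.1²/90² = 58.4, so 59 by normal approximation and 61 by t-test.
- Non-centrality with 30: 90/212.1 × √30 = 2.32. Power is 61.2% (t) or 64.2% (normal).
- If all 36 complete: 69.6% (t).
- Standard error with 30: 212.1/√30 = 38.7 mL. The 95% CI half-width is about 2.05 × 38.7 = 79 mL.
- Difference detectable with 90% power: about 130 mL (t) or 126 mL (normal).

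**Step 3. Do other choices close the gap?**

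| Assumption | SD_d (mL) | Power, 30 completers (t) | Power, 36 completers (t) | n for 90% (t) |
|---|---|---|---|---|
| σ_w = 150 mL, as labelled | 212.1 | 61.2% | 69.6% | 61 |
| σ_w = 150 mL, one-sided test | 212.1 | 73.3% | – | – |
| σ_w = 114 mL, the cohort figure | 161.2 | 83.9% | 90.2% | 36 |
| SD_d = 150 mL (σ_w ≈ 106 mL) | 150 | 88.7% | 93.8% | 32 |

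Neither the choice between t and normal (3 points) nor a one-sided test explains a shortfall of 26 to 29 points. With the cohort's smaller 114 mL as the within-subject SD, 30 completers still fall short of 90%.

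**Step 4. Another route to 30.** The total of 58.4 from step 2, halved, is 29.2 per sequence, which rounds up to 30. The printed number could therefore also be a per-sequence figure reported as a total. The text alone cannot separate this from the reading in step 1.

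**The case against.** The strongest reply is that 150 mL is loosely labelled and the calculation itself is sound. If the cohort supplied one change per patient (an assumption; the article does not say), the SD seen across patients is the total SD of a single change, made up of between- and within-subject variance. Splitting 150 mL equally gives a within-subject SD of 106 mL and a treatment-difference SD of 150 mL. The normal formula then returns 29.2, rounded to 30, with 90.8% power. This uses every input in the paragraph, including the ratio. On that reading, 36 completers would give 93.8% by t-test, and the cohort's 114 mL would give 98.7% with 30.

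Much of this stands. The reading is plausible, it leads to the same numbers as treating 150 mL as the SD of the paired difference, and it means that actual underpowering is not shown. It is also fair that planning on 150 mL in place of an observed 114 mL is a cautious step on any reading, so the description of the SD as conservative is not at fault.

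It does not rescue the paragraph. A between-subject SD is neither a total SD nor the SD of a paired difference, and the text gives a separate ratio linking it to the within-subject SD. The per-sequence explanation also yields 30 and would mean that the sample is half what was intended. The article is a condensed account, and a fuller protocol or analysis plan may define the SD properly. Even so, this paragraph prints all its inputs and its result, and they disagree.

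**Conclusion.** The concern holds. From the SDs as labelled, 30 completers give about 61% power to detect 90 mL, against a stated 90%, and about 61 completers would be needed. The result rests on a standard 2×2 crossover comparison, a two-sided 5% test, and a within-subject SD of 150 mL taken from the stated SD and ratio.

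The inconsistency is certain; which element is wrong is not. If 150 mL is the SD of the within-patient difference, or a total SD split equally, the label is at fault and true power is about 89%. If the within-subject SD really is 150 mL, the power statement overstates by nearly 30 points. The two outcomes differ enough that the paragraph must be corrected. The allowance from 30 to 36 for dropout is not in question.

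**What to change.** Check the within-patient SD in the cohort data, then correct the paragraph to match, without changing the sample size:

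- **If 150 mL is the SD of the within-patient treatment difference** (or a total SD split equally between and within patients): say so, give the within-subject SD as about 106 mL, and state about 89% power with 30 completers by t-test. If the 90% figure is kept, name the normal approximation.
- **If the within-subject SD is 150 mL:** state about 61% power with 30 completers (70% with 36) and a 90%-detectable difference of about 130 mL.

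In either case, name the formula used and say whether 30 is a total or a per-sequence number.

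The cost is one reworded paragraph in the protocol, and in the analysis plan if it repeats the calculation. No extra patients are needed and the design and analysis do not change. The price is that the stated power may become less favourable.

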### Statistical analysis

Two different analysis sets, namely the full and safety analysis sets (FAS and SAS, respectively), will be used in the study. The FAS will include all study participants who receive at least one dose of the study drug and complete at least one post-baseline examination or assessment. The SAS will include all the study participants who receive at least one dose of the study drug. Analyses of the primary and secondary endpoints excluding adverse events will be conducted in the FAS. Adverse events will be compared between the two groups in the SAS. To assess the effects of empagliflozin versus placebo on the primary outcome, we will use a mixed-effects model for repeated measures (MMRM). The model includes treatment, period, and treatment-by-period interaction as fixed effects and individual as random effects. An unstructured marginal covariance structure will be specified. Secondary endpoints for continuous variables will be estimated in the same manner as described for primary endpoints excluding urine KIM-1. In the case of urinary KIM-1, the analysis using MMRM will be conducted with the absolute value at the end of each period as the dependent variable. Skewed data will be log-transformed before analyses. A list of adverse events will be summarized by tables for each treatment. For sensitivity analyses, we will employ a similar analysis by excluding the data with catheter dysfunction (i.e., drainage volume < 80% of the instilled volume or taking ≥ 20 min to instill the PD solution). A subgroup analysis will be performed using the following factors: age (< 65 years/ ≥ 65 years), sex, presence or absence of diabetes, use of icodextrin-containing PD solution, 24-h urine volume (< 200 mL/ ≥ 200 mL), the glucose load from the peritoneal dialysate (concentration × volume per day, median), the glucose concentration of the drained PD solution on FAST PET (median), and the drained PD solution-to-serum creatinine ratio (median) on FAST PET. Missing data will not be imputed. Statistical analyses will be performed using SAS software (SAS Institute, Cary, NC, USA). Interim analysis will not be conducted.

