## Introduction

Peritoneal dialysis (PD) is an established renal replacement therapy, based on the exchange of water and solute between capillary blood and dialysate fluid across the peritoneal membrane, and 11% of patients undergoing dialysis worldwide are on PD [1]. Given the link between volume overload and poor outcomes, encompassing both technical survival and mortality in patients on PD [2], adequate ultrafiltration, relying on the osmotic gradient typically induced by the hypertonic glucose concentration, is a crucial element for successful PD therapy. Ultrafiltration and the volume status are closely interrelated, and in fact, several studies reported that higher ultrafiltration volume was associated with better prognosis in patients on PD [3, 4]. The glucose gradient peaks at the start of dialysis but diminishes as glucose diffuses into blood. In patients with greater peritoneal vascularity in particular, it is difficult to achieve adequate ultrafiltration because the glucose gradient diminishes more rapidly [5]. One typical strategy in this setting is to use a PD solution with higher glucose content to obtain a higher glucose gradient. However, this strategy might be ineffective because of enhanced fluid intake attributable to hyperglycemia, and it can lead to more rapid damage to the peritoneal membrane, resulting in the discontinuation of PD therapy [6].

Recent studies confirmed the expression of sodium–glucose cotransporter 2 (SGLT2) in the human peritoneum [7–9]. Animal studies demonstrated that SGLT2 inhibitors increased ultrafiltration potentially through the maintenance of the glucose gradient upon the inhibition of SGLT2 activity in the peritoneum, although conflicting results exist [7, 9, 10]. In addition, SGLT2 inhibitors were reported to mitigate peritoneal fibrosis and angiogenesis, both of which contribute to ultrafiltration failure, in a mouse model [8, 11]. Based on this information, we hypothesized that SGLT2 inhibitors might increase the ultrafiltration volume and improve long-term prognosis in patients on PD by correcting volume overload and mitigating peritoneal tissue damage. Because there is little information on the use of SGLT2 inhibitors in patients on PD, we decided to first evaluate the effect of SGLT2 inhibitors on the ultrafiltration volume in short-term interventions.

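### Three continuous subgroup factors are cut at the sample median in 30 to 36 patients; continuous terms would use the same data more efficiently

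*Protocol article*

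**What the plan says.** The Statistical analysis section of the protocol article names eight subgroup factors. Five are categories or have fixed cuts: "age (< 65 years/ ≥ 65 years), sex, presence or absence of diabetes, use of icodextrin-containing PD solution, 24-h urine volume", the last of these divided at 200 mL. The other three are marked for a cut at the median, with no numeric value:

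- "the glucose load from the peritoneal dialysate (concentration × volume per day, median")
- "the glucose concentration of the drained PD solution on FAST PET (median")
- "the drained PD solution-to-serum creatinine ratio (median) on FAST PET"

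The section announces a subgroup analysis on these factors. It states neither an interaction test nor a model with any of the three kept continuous.

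On numbers, the Sample size calculation section says that "30 patients completing the study would provide 90% power (at α = 0.05, two-sided") to detect 90 mL, and that "The sample size was set at 36 subjects to compensate for potential dropouts".

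On background, the Introduction says: "In patients with greater peritoneal vascularity in particular, it is difficult to achieve adequate ultrafiltration because the glucose gradient diminishes more rapidly". The Discussion suggests that the drug might raise ultrafiltration by preserving that gradient.

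**The concern.** All three factors are continuous and bear on glucose exposure or transport across the membrane, where the article looks for the drug's mechanism. If the effect changes gradually with such a factor, a two-group split describes it poorly. A patient just above the median counts the same as the most extreme patient, while two nearly identical patients on either side of the cut count as different. Because the cut-point comes from this sample, a result for the upper half does not carry over to patients elsewhere.

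At stake is the precision of an exploratory answer to who benefits more. With about 15 to 18 patients per half, a real gradient is easily missed, and the split makes that more likely if the gradient is roughly linear.

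**Working it through.** **Inputs from the article (Sample size calculation):** 30 completers, 36 randomized, target difference 90 mL, two-sided α = 0.05, power 90%, SD 150 mL.

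**Inputs that are assumptions:** the distribution of each factor, the shape and steepness of any effect modification, and 150 mL as the SD of the within-patient treatment difference.

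**1. The plan's own figure.** For a within-patient comparison, n = [SD × (z₀.₉₇₅ + z₀.₉₀) / 90]² = [150 × (1.960 + 1.282) / 90]² = 29.2, rounded up to 30. The stated number reproduces if 150 mL is the SD of the within-patient difference, so that value is used below. If instead the between-subject SD is 150 mL and the 1:1 ratio gives a within-subject SD of 150 mL, the SD of the difference is √2 × 150 = 212 mL. The power figures below would then be lower; the information loss would not change.

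**2. Information kept by a median split.** With a linear effect, the fraction kept is the squared correlation between the factor and its high/low indicator. For a normal factor this is 2/π = 0.637, so the loss is 1 − 0.637 = 36.3%. Simulation with the sample median gives 36.3% at n = 30 and 36.4% at n = 36. In patients, 30 × 0.637 ≈ 19 and 36 × 0.637 ≈ 23 analysed continuously would be as informative.

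**3. Dependence on the distribution** (simulated at n = 30 and 36, effect linear on the factor's own scale):

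| Distribution of the factor | Loss |
|---|---|
| Bimodal | about 20% |
| Uniform | about 27% |
| Normal | about 36% |
| Log-normal, log-SD 0.3 to 0.5 | 39-45% |
| Exponential | about 48% |
| Log-normal, log-SD 1 | about 60% |
| Any, with a true step at the median | nil |

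If a log-normal factor acts linearly on the log scale, the normal row applies.

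**4. Precision of the split** (SD of the difference 150 mL).

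- 95% CI half-width within one half: 1.96 × 150/√15 = 76 mL at n = 30, and 1.96 × 150/√18 = 69 mL at n = 36.
- Standard error of the contrast between halves: 2 × 150/√n = 54.8 mL and 50.0 mL.
- Contrast detectable with 80% power: (1.960 + 0.842) × SE = about 153 mL and 140 mL. Both exceed the 90 mL that the whole trial targets.

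**5. Power to detect effect modification** (normal factor, linear effect, test at 0.05 two-sided on the within-patient difference, 20,000 replicates, n = 30):

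| Assumed gradient, mL per SD of the factor | Continuous | Median split |
|---|---|---|
| 30 | 18% | 13% |
| 45 | 35% | 24% |
| 60 | 54% | 36% |
| 82.5 (0.55 × 150) | 79% | 57% |

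Repeated runs differ by about one percentage point. At n = 36 and 60 mL per SD the figures are 62% and 43%.

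**6. The opposite case.** If the modification is a step at the median of ±60 mL, the split does better: at n = 30, 56% against 37% for the linear term (3,000 replicates).

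**The case against.** The strongest reply is that this is a conventional descriptive subgroup display in a small trial. Median halves are balanced and insensitive to outliers, and the rule is fixed in advance, so the cut cannot be chosen after seeing results. A linear slope in 30 patients leans on its extreme values and on linearity. The article is a condensed document, and an analysis plan not shown may already hold continuous models. At moderate gradients both methods are weak, so the small sample is the main limit.

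Most of this stands, and it sets the point's weight. It does not remove the point: the median cut is stated, and a continuous term can be added without giving up the display.

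A reader might infer more than the article supports in four ways:

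- **That 36% of the information is lost, as a fact about this trial.** That figure needs a normal factor and a linear effect, and the article gives neither. Eligibility requires at least 3 L/day of glucose-based solution, which truncates volume and makes normality doubtful for glucose load.
- **That power falls from 79% to 57%.** This assumes 82.5 mL per SD. With a mean effect of 90 mL, the effect would run from 7.5 mL at one SD below the mean to 172.5 mL at one SD above. Nothing in the article supports so steep a gradient.
- **That effect modification is the trial's main question after the primary.** The Abstract names other key secondary endpoints, and the Statistical analysis section announces only a subgroup analysis.
- **That the Introduction presents these three variables as the drug's route of action.** It speaks of the glucose gradient, and explains why ultrafiltration is hard in one group of patients. It does not state a graded treatment effect.

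**Conclusion.** The point holds as a minor one. The plan fixes a sample-dependent cut on three continuous factors where a more efficient analysis of data already collected is available. The benchmark loss is about 36% for a normal factor with a linear effect, about 20% to 60% over the other distributions examined, and nil for a step at the median. For assumed gradients of 45 to 60 mL per SD, with an assumed 150 mL SD of the within-patient difference and 30 patients, power is about 35-54% with a continuous term against 24-36% with the split.

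Neither approach makes these exploratory analyses strong, and an absence of apparent effect modification should not be read as evidence against it. The primary result, the sample size and the safety analyses are untouched.

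**What to change.** For each of the three factors, add the baseline value as a continuous covariate, with its interaction with treatment, to the planned mixed model, one factor at a time. Use one value per patient from before the first treatment period, so that the modifier cannot itself be affected by treatment. Log-transform a skewed factor. Report the slope with its 95% CI and the predicted treatment effect at the quartiles, and check linearity with a plot of within-patient differences against the factor. Keep the median-split estimates as a descriptive display and report the cut-points found. Write this down before unblinding, unless the analysis plan already contains it.

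The cost is a short passage in the analysis plan and three further model fits. No visit, measurement or sample size changes. The downside is reliance on approximate linearity and sensitivity to extreme values, which the plot and the retained split help to reveal.

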## Discussion

A large amount of evidence supports the use of SGLT2 inhibitors in individuals with heart failure or chronic kidney disease (CKD) [13, 14]. However, few studies have examined treatment with SGLT2 inhibitors in patients with advanced CKD, especially those requiring dialysis. Because SGLT2 is expressed somewhat specifically in renal tubules [15], it is theoretically possible that the effectiveness of SGLT2 inhibitors could diminish as renal function worsens. On the contrary, emerging data indicate that the cardiovascular and kidney benefits of SGLT2 inhibitors do not wane even as the estimated glomerular filtration rate (eGFR) declines at least in patients with eGFR ≥ 20 mL/min/1.73 m^2^ [16, 17]. Furthermore, in the DAPA-CKD study (trial registration: NCT03036150), in which patients continued taking the study drug after starting renal replacement therapy, dapagliflozin achieved a 21% relative risk reduction in mortality within the subset of patients who commenced dialysis therapy (unpublished data described in the rationale for the RENAL LIFECYCLE Trial [18]). These observations raise the possibility that SGLT2 inhibitors can exert their organ-protective effects through mechanisms distinct from merely blocking SGLT2 in renal tubules.

The current trial was prompted by a report in 2019 that SGLT2 is expressed in the human peritoneum [7]. If SGLT2 plays a role in glucose absorption from the PD solution, SGLT2 inhibitors might enhance the ultrafiltration volume by preserving the glucose gradient across the peritoneum membrane. Although animal studies have yielded inconsistent results [7, 9, 10], recent human case series reported the positive effects of SGLT2 inhibitors on the ultrafiltration volume [19, 20]. Therefore, we planned to conduct a clinical trial evaluating the impact of SGLT2 inhibitors on the ultrafiltration volume. To the best of our knowledge, only two other small randomized, controlled trials (RCT) are currently investigating the effects of SGLT2 inhibitors in patients on PD. One of these trials is an open-label RCT involving 36 patients with type 2 diabetes on PD assessing BNP as the primary endpoint (trial registration: jRCT1011210022). The other trial is a double-blind, placebo-controlled, crossover RCT with 30 patients on PD, and the primary endpoint is glucose absorption from the PD solution (trial registration: NCT05671991). Notably, our trial is particularly unique in that the primary endpoint is the daily ultrafiltration volume, which is an important indicator for patients on PD [3, 4], and the impact on residual renal function will be evaluated. These ongoing RCTs are expected to furnish robust evidence regarding the efficacy and safety of SGLT2 inhibitors in patients on PD.

